### Measures

Educators (principals/administrators, teachers, paraeducators) will complete secure web-based surveys via REDCap at three time points (Table 1). Time points will be baseline (April/May; T1) before the academic year in which schools will receive HELM, winter (Jan/Feb; T2, 8–9 months after baseline), and spring of the subsequent year (April/May; T3, 12 months after baseline). Educators will self-report their demographic characteristics, organizational mechanisms of change (implementation leadership and climate), implementation time and costs, and deidentified classroom-level outcomes. Educators will be compensated $40 for the completion of study instruments at each data collection timepoint.

**Table 1 Tab1:** Study Measures

Construct	Measure Description	Source	Time
School demographics	School size, student body racial/ethnic composition, % free/reduced lunch	A	T1
	**Organizational Mechanisms**		
Implementation Leadership	*School Implementation Leadership Scale* (SILS; 15): Adapted from the original ILS [20], the SILS has 24 items loading onto 8 subscales: Proactive, Knowledgeable, Supportive, Perseverant, Communication, Vision, Available, and Distributed Leadership. Subscale internal consistencies range from 0.91 to 0.96, and scores correlate with other leadership measures	P DLT T	T1-T3
Implementation Climate	*School Implementation Climate Scale* (SICS; [48]): Adapted from the original ICS [21] includes 21 items loading onto 7 subscales: Focus on EBP, Educational Support for EBP, Recognition for EBP, Rewards for EBP, Use of Data to Support EBP, Existing Supports for EBP, and EBP Integration, with good internal consistency estimates (range: 0.81–0.90)	P DLT T	T1-T3
Burnout	*Maslach Burnout Inventory* (MBI; [49]): Burnout will be measured using the 22-item MBI. Respondents will use a 7-point Likert (“0-Never” to “6-Every Day”) to respond to items across three subscales: nine items measure emotional exhaustion (e.g., “I feel used up at the end of my workday”), five items measure depersonalization (e.g., “I feel I treat some students as if they were impersonal objects”), and eight items measure personal accomplishment (e.g., “I deal very effectively with the problems of my students”). Internal consistency was acceptable for burnout (α = .89), emotional exhaustion (α = .91), and personal accomplishment (α = .83). The lower estimate for depersonalization (α = .69) is consistent with extant research using the MBI-ES [50]	P DLT T	T1, T3
Implementation Citizenship Behavior	*Implementation Citizenship Behavior Scale (*ICBS; [51]): The School Implementation Citizenship Behavior Scale is a 12-item scale with four subscales. This study will evaluate 6 items loading onto 2 subscales: Helping Others and Keeping Informed. Research demonstrates acceptable reliability (αs = .88-.92) for all subscales	P DLT T	T1-T3
Coordination	*Team Process Scale (TPS): Coordination* [52]: Team-related processes will be measured using the 5-item Coordination response scale of the TPS. Respondents will use a 5-point Likert (“0 = not at all to 5 = to a very great extent”) to report the extent to which they perceive their team engages in effective team processes. Research supports the content and construct validity of several versions of this scale, including the 5-item Coordination response scale.	P DLT	T1-T3
Change Fatigue	*Change Fatigue* [53]: This 6-item validated measure will be used to measure the impact of organizational change on employee outcomes (e.g. well-being, withdrawal, organizational commitment, turnover intentions).	P DLT T	T1, T3
	**Implementation Outcomes**		
PBIS Fidelity	The *Tiered Fidelity Inventory* (TFI; [54]) is a 45-item tool used to provide a valid, reliable, and efficient measure of the extent to which school personnel are applying the core features of PBIS. The TFI is a group-assessment completed by a schoolwide system planning team with external facilitation with strong internal consistency (α = .96). The TFI will be collected for both PBIS + HELM and PBIS + IAU conditions across the three time points	P DLT T O	T1-T3
Implementation Cost	Costs of 1) delivering HELM to augment PBIS implementation, as well as 2) IAU, will be calculated using activity-based cost metrics. Inputs will include time, supplies, travel, overhead, and costs associated with HELM training/coaching meetings, including pre-work, scheduling, and attending meetings; as well as costs associated with PBIS training and delivery in each study condition.	A P DLT T	T1-T3
	**Behavioral and Academic Outcomes**		
Academic engagement; Prosocial behavior; & Problem behavior	*Modified Direct Behavior Rating (DBR)* will be used in which teachers observe and rate their classroom’s overall academic engagement (i.e., actively or passively participating in the classroom activity, 0–100%), disruptive behavior (i.e., interrupting activities, 0–100%), and prosocial behavior (i.e., following directions, 0–100%; Chafouleas et al., 2012). The DBR is sensitive to behavior change [55, 56] and is more feasible than assessing individual students.	T	T1-T3
Educational and Behavioral Outcomes	Standardized academic test scores, attendance rates, and disciplinary incidents (office discipline referrals, suspensions, expulsions) will be derived from administrative records	A	T1 -T3
	**HELM Manipulation Check**		
HELM Fidelity	Coding of video recordings of HELM delivery	O	T1 -T3

Note: *A* Administrative data, *P* Principal, *DLT* distributed leadership team, *T* Teacher, *O* Trained observer; T1 = Baseline (Apr/May prior to HELM/PBIS delivery year), T2 = Jan/Feb, 9 months after baseline, T3 = Apr/May, 12 months after baseline

*Fidelity*. The study’s primary outcome is school-level PBIS fidelity, assessed using the Tiered Fidelity Inventory (TFI; [54]). Facilitated by an expert PBIS coach, school PBIS implementation teams will complete the TFI in both the HELM and control conditions. The TFI is designed to be used 1) for initial assessment to determine the degree to which a school is using PBIS-consistent practices; 2) as a guide for implementation of Tiers 1, 2, and 3 EBPs, and 3) to track PBIS implementation over time. TFI data will be collected at the same time points as educator data.

*HELM fidelity checklist*. This checklist will be used as a manipulation check to document HELM delivery (based on observations of recorded HELM trainings). HELM coaches will complete a standardized measure of dates specific steps were completed.

*Qualitative Focus Groups*. We will develop a systematic, comprehensive semi-structured focus group guide that draws from the EPIS framework to examine multilevel (i.e., intervention, individual, inner, and outer settings) determinants that explain what processes facilitated or hindered implementation [28]. We will generate questions that explore the most salient implementation determinants and mechanisms, and how implementation leadership and climate may interact with other relevant characteristics of the setting [57, 58].

*Administrative Data*. At the end of each school year, deidentified academic records by classroom will be requested for all participating schools to extract students’ attendance, discipline (office disciplinary referrals), and achievement (grades, standardized test scores). To assist in modeling, these data will be collected retrospectively for the year prior to HELM participation as well as each cohort’s HELM year.

*Cost Assessments*. Activity-based costing will be used to comprehensively estimate the costs of HELM and the comparison condition [59, 60]. We will measure cost from the payor (i.e., school system) perspective, since the primary costs and associated decision-making are within the implementing school district [61]. We will isolate costs of HELM as an implementation strategy, but since HELM may have secondary impacts on PBIS costs – e.g., by increasing educator engagement in implementation – we will measure and monetize differences between study conditions in costs related to teachers’ participation in PBIS training, consultation, and delivery.

We will include open-ended items in each survey that ask about unexpected resources needed for HELM and/or PBIS. Using a sequential qual → QUANT development function, we will rapidly analyze responses on an ongoing basis so that we can immediately incorporate any newly identified cost categories into future surveys for quantitative measurement [62, 63]. To assign cost values to categories that are measured in non-monetary values (e.g., trainer time delivering HELM, teacher time spent on PBIS), we will use other data sources such as school district records or project expense reports.

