**Methods:**

This study will use a hybrid type 3 effectiveness-implementation trial to provide a rigorous test of the effects of HELM in elementary schools. Schools will be randomly assigned to HELM + PBIS training and technical assistance (*n* = 21 schools; n = 210 educators) or PBIS training and technical assistance only (*n* = 21 schools; n = 210 educators) in a 1:1 ratio within cohorts using covariate constrained randomization that accounts for degree of prior PBIS exposure (measured using the Tiered Fidelity Inventory at baseline) and school size. A series of mixed effects models (time within educator, educator within school) will test within-subject/between-subject interactions across three timepoints (12 months total) to examine whether HELM will show steeper gains than the control on implementation leadership (primary outcome), implementation climate, PBIS fidelity, and student outcomes. Mediational analyses will test hypothesized mechanisms of change (i.e., implementation leadership and climate) of HELM on PBIS fidelity. Sequential mixed-methods data collection and analyses will further explore how organizational mechanisms are linked to implementation outcomes. Cost-effectiveness analyses will compare costs and outcomes of PBIS training and technical assistance only versus PBIS implementation with HELM.

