## Study purpose and aims

The purpose of this study is to test the effectiveness of HELM on school-wide implementation of PBIS (i.e., fidelity) relative to a PBIS training and technical assistance condition. Experimental and exploratory aims are:

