### Aim 1: Experimentally evaluate the effects of HELM.

Hypothesis 1a. Schools randomized to HELM will demonstrate higher PBIS fidelity compared to schools randomized to PBIS training and technical assistance only (control schools).

Hypothesis 1b. Schools randomized to HELM will demonstrate greater improvement in school context factors that support implementation (i.e., implementation leadership, implementation climate) compared to control schools.

Hypothesis 1c. Students in schools randomized to HELM will demonstrate improved social, emotional, and behavioral and academic outcomes compared to students in control schools.

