### Aim 2: Explore for whom, under what conditions, how equitably, and through which processes HELM works to improve outcomes, as well as its cost-effectiveness.

Research Question 2a. Are the effects of HELM on PBIS fidelity mediated by improvement in organizational mechanisms of change (i.e., implementation leadership and climate)?

Research Question 2b. Are the effects of HELM on student outcomes mediated via implementation outcomes (i.e., PBIS fidelity)?

Research Question 2c. Are the effects of HELM consistent and equitable across buildings or are they moderated by school contextual factors (e.g., school size, student body racial/ethnic diversity, free/reduced price lunch)?

Research Question 2d. What explains implementation success in schools where HELM’s explanatory model does not fit? What factors outside of the hypothesized mechanisms explain implementation success (i.e., high fidelity) in schools where HELM’s explanatory model does fit?

Research Question 2e. What are the costs and cost-effectiveness of HELM vs. PBIS implementation as usual?

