All analyses will use an intent-to-treat approach in which units are analyzed based on condition assignment regardless of HELM implementation success [75]. Because the trial includes outcomes at multiple levels, the specific analytic approach will vary depending on the outcome. However, in general, analyses will employ 2- or 3-level mixed effects models reflecting data collection time points nested within educator/classroom nested within schools. We will test for significantly large ICCs at the district levels to determine if statistical nesting is necessary. Standard model-building procedures will be used [76, 77], including fitting a null model to facilitate calculation of variance accounted for in later models, fitting unconditional growth models (e.g., linear, quadratic, piecewise) to determine the optimal functional form for time, and finally, fitting models that include the variable for condition (and the condition by time interaction, as appropriate) along with covariates. Iterative models with possible covariates will be tested. Covariates not significantly contributing to the model at *p* < 0.10 based on likelihood ratio tests will be removed. We will obtain estimates of whether there were statistically significant differences between conditions on rate of change over time (i.e., slope), and whether there are statistically significant condition differences in average score on each outcome at T2 and T3. Models will be generalized, with appropriate link functions (e.g., log-link, Poisson) applied based on distributional form (e.g., dichotomous, zero-inflation). Estimations will be fit using full maximum likelihood. Models will be assessed for possible violations of assumptions. Inference will be evaluated relative to *p* < 0.05. For hypotheses/research questions with multiple DVs, we will adjust for familywise error using Benjamini and Hochberg’s False Discovery Rate [78].

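### The article names two different primary outcomes, implementation leadership in the Abstract and PBIS fidelity in Measures, and its multiplicity rule does not cover the two together

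*Protocol article*

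**What the plan says.** In the protocol article, the Methods part of the Abstract says the mixed models will examine whether HELM shows "steeper gains than the control on implementation leadership (primary outcome), implementation climate, PBIS fidelity, and student outcomes". The primary label is on leadership; fidelity comes later in the list without it.

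In Measures, the Fidelity paragraph after Table 1 says the study's "primary outcome is school-level PBIS fidelity, assessed using the Tiered Fidelity Inventory".

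Other sections bear on which was meant:

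- **Study purpose and aims:** "The purpose of this study is to test the effectiveness of HELM on school-wide implementation of PBIS (i.e., fidelity".
- **Hypothesis 1a (Aim 1):** "Schools randomized to HELM will demonstrate higher PBIS fidelity compared to schools randomized to PBIS training and technical assistance only".
- **Hypothesis 1b (Aim 1):** "greater improvement in school context factors that support implementation (i.e., implementation leadership, implementation climate".
- **Research Question 2a (Aim 2):** "Are the effects of HELM on PBIS fidelity mediated by improvement in organizational mechanisms of change (i.e., implementation leadership and climate".
- **Abstract, Background:** the purpose is given as promoting leadership, climate and high-fidelity delivery, in that order.

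On error control, the Data Analytic Approach states: "Inference will be evaluated relative to *p* < 0.05". It applies Benjamini-Hochberg where one hypothesis or research question has several dependent variables. For each outcome it plans a slope comparison and condition differences at T2 and T3, without ranking them. The Power Analysis gives one range of detectable effects, 0.23 to 0.65, for outcomes at all levels.

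**The concern.** A confirmatory trial needs one stated test, or a stated set of tests, on which success is judged. Here the article gives two answers, and the choice changes the test. Fidelity is a school-level team score and the only dependent variable of Hypothesis 1a, so it is tested at 5% without adjustment. Leadership is rated by about 420 educators and shares Hypothesis 1b with climate, so it is adjusted.

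Leadership is also what HELM trains directly and feeds back to schools, and it is the proposed mediator of the effect on fidelity. A report following the Abstract could call the trial positive on leadership with no effect on fidelity, while a report following Measures could not. If the choice were settled only after results, it could not be told apart from outcome switching.

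**Working it through.** **1. Is there any reconciling text?** The Abstract says leadership and Measures says fidelity, in the singular. No section describes co-primaries, a hierarchy or a gatekeeping order. Study purpose and aims, Hypothesis 1a and Research Question 2a fit fidelity as the endpoint with leadership as mechanism, and Table 1 also lists leadership under organizational mechanisms. The Abstract's Background, with leadership first, points weakly the other way.

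**2. Does the multiplicity rule cover both?** Fidelity is in 1a; leadership and climate are in 1b. Benjamini-Hochberg is applied within a hypothesis, so it joins leadership with climate but not with fidelity.

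**3. Error rate if either outcome may carry the claim.** One test per outcome is counted, with all nulls true.

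*Leadership adjusted with climate (two tests, independent).* Leadership is rejected if its p ≤ 0.025, or if its p lies between 0.025 and 0.05 and climate's p ≤ 0.05:

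0.025 + 0.025 × 0.05 = 0.02625

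Either fidelity or leadership, independent: 1 − 0.95 × (1 − 0.02625) = 1 − 0.92506 = 0.0749, about 7.5%.

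*Both at a full 5%, independent:* 1 − 0.95² = 0.0975. This applies, for example, when climate has a real effect and is rejected, which leaves leadership at 0.05.

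*Both at a full 5%, correlated (simulation, 2 million draws):*

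| Correlation | Either significant |
|---|---|
| 0.5 | 9.1% |
| 0.7 | 8.3% |
| 0.9 | 7.0% |

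With one primary fixed in advance the rate is 5%.

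**4. Which detectable effect belongs to the primary?** The stated range of 0.23 to 0.65 cannot be reproduced exactly, because neither the power level nor the assumptions per outcome are given. From the Power Analysis: 42 schools and 50% of posttest variance explained by pretest. Assumed here: 80% power and two-sided 5%. For a school-level score:

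MDES = (t₀.₉₇₅ + t₀.₈₀) × √(4(1 − R²)/J)

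- J = 42: about 2.874 × √(4 × 0.5/42) = 2.874 × 0.2182 = 0.627.
- J = 40 (one school lost per condition): 0.643.
- Power at an effect of 0.65 with 42 schools: 83% (t) to 85% (normal approximation).

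The upper end of the stated range is therefore compatible with fidelity as a school-level outcome, but the article does not say that it is that outcome's figure.

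**5. If the two were alternative primaries at 0.025 each.** The fidelity MDES becomes about 0.69 with 42 schools, above the stated upper end of 0.65.

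**The case against.** Nobody can fairly dispute that the two sentences disagree. The case on the other side concerns how much follows from that, and most of it stands.

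- **A reader might infer that the trial has no fixed primary outcome.** The article reports prospective registration on August 27, 2024. That record is not available here and may settle the matter. What is shown is that the article contradicts itself.
- **A reader might infer that the error rate nearly doubles to 9.75%.** That is an upper bound. It ignores the article's own adjustment of leadership with climate and assumes independence, which sits badly with a theory of change in which leadership drives fidelity. The excess over 5% remains, but the size depends on these conditions.
- **A reader might infer that leadership is much easier to detect.** The same inputs give 0.27 to 0.40 for leadership (10 educators per school, ICC 0.10 to 0.35) against 0.63 for fidelity. The first is in SDs of individual educator scores and the second in SDs of school scores. Dividing by the SD of a school mean, 0.273/√0.19 and 0.404/√0.415 both give about 0.627. The comparison shows no power advantage.
- **A reader might infer that fidelity at T3 must be the primary.** The text favours fidelity but does not settle it, and the analysis section ranks none of slope, T2 and T3. Choosing T3 would be a new decision.

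**Conclusion.** The point holds as an internal contradiction: the article names two primary outcomes and reconciles them nowhere. This rests on the text alone and on none of the calculations. PBIS fidelity on the TFI is the better-supported reading, not an established one.

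The article does fix a per-test threshold and a rule within each hypothesis. It does not consistently identify the test that carries the confirmatory claim, and it sets no error control across fidelity and leadership. If success could be claimed on either, the false-positive rate would be about 7.5% under the article's own adjustment (independent tests, all nulls true) and at most 9.75% (both at a full 5%, independent). Positive correlation between the two outcomes lowers these figures. Allowing a choice among slope, T2 and T3 as well would add to them; that is not counted here.

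The detectable effect of about 0.63 school-level SD for fidelity rests on 42 schools, R² 0.5 and the assumed 80% power and two-sided 5%. The correction should be made before enrolment.

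**What to change.** Before the first cohort is enrolled:

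1. Compare the Abstract and the Fidelity paragraph of Measures with the registered primary outcome. If the registry names the outcome that is not kept, record this openly as a change to the registered primary.
2. Name one primary outcome in the same words in the Abstract, Measures and Power Analysis, and list the other as secondary. PBIS fidelity on the TFI, with leadership and climate as secondary mechanism outcomes, is the reading that best fits the text. If both were intended, declare co-primaries and give the alpha rule: whether both must succeed, or how 5% is shared if either suffices.
3. Name the primary contrast: slope, T2 or T3.
4. State which detectable effect within 0.23 to 0.65 belongs to the primary outcome, in which SD units, and at what power and sidedness.

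Items 1, 2 and 4 are mostly wording, though declaring co-primaries would need an alpha rule and possibly a revised power statement. Item 3 is a real decision but needs no new data. The Discussion reports that no participants had been enrolled as of February 2025, so on that date none of this touched collected data.

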**Fig. 2 Fig2:**
[figure not shown]
HELM mediational model: RQ2a

*Data Analytic Approach*. We will explore for baseline equivalence between conditions on all school, teacher, and student variables following Institute of Educational Sciences guidelines, with effect sizes between 0.05 and 0.25 indicating that statistical adjustment for nonequivalent baseline characteristics is required [73]. Non-equivalent baseline characteristics will be included as covariates at the school, educator, or student level, as appropriate. Following best practice guidelines, variables used for covariate constrained randomization will be included as covariates in all models [46, 74]. Data missing at random will be modeled using full information maximum likelihood estimation in mixed effects modeling or multiple imputation for other analyses. Although all analyses will use an intent-to-treat approach, we will examine the robustness of condition assignment through descriptive analyses of scores on the HELM fidelity tools. Schools that achieve 80% or higher of the maximum possible score on all HELM fidelity criteria will be considered having received a full dose of HELM training and coaching.

All analyses will use an intent-to-treat approach in which units are analyzed based on condition assignment regardless of HELM implementation success [75]. Because the trial includes outcomes at multiple levels, the specific analytic approach will vary depending on the outcome. However, in general, analyses will employ 2- or 3-level mixed effects models reflecting data collection time points nested within educator/classroom nested within schools. We will test for significantly large ICCs at the district levels to determine if statistical nesting is necessary. Standard model-building procedures will be used [76, 77], including fitting a null model to facilitate calculation of variance accounted for in later models, fitting unconditional growth models (e.g., linear, quadratic, piecewise) to determine the optimal functional form for time, and finally, fitting models that include the variable for condition (and the condition by time interaction, as appropriate) along with covariates. Iterative models with possible covariates will be tested. Covariates not significantly contributing to the model at *p* < 0.10 based on likelihood ratio tests will be removed. We will obtain estimates of whether there were statistically significant differences between conditions on rate of change over time (i.e., slope), and whether there are statistically significant condition differences in average score on each outcome at T2 and T3. Models will be generalized, with appropriate link functions (e.g., log-link, Poisson) applied based on distributional form (e.g., dichotomous, zero-inflation). Estimations will be fit using full maximum likelihood. Models will be assessed for possible violations of assumptions. Inference will be evaluated relative to *p* < 0.05. For hypotheses/research questions with multiple DVs, we will adjust for familywise error using Benjamini and Hochberg’s False Discovery Rate [78].

*Qualitative Analysis.* Certain codes will be conceptualized during the protocol guide development and driven by the EPIS framework (i.e., deductive approach) and others will be developed through reading an initial subset of transcripts (i.e., inductive approach). Themes will provide a way of understanding the most salient factors that impact implementation and extend beyond the existing HELM organizational mechanisms and theory of change [79, 80]. EPIS-driven directed coding will include system levels (i.e., intervention, individual, inner setting, outer setting) as initial “parent nodes.” After a stable set of codes is developed, a consensus process will be used in which all reviewers independently code and compare their coding to arrive at consensus judgments through open dialogue [81–83].

*Cost and Cost-Effectiveness Analyses*. We will use the CostOut program to complete the cost analysis for HELM and PBIS implementation-as-usual. CostOut specifies ingredients for each intervention condition, assigns prices (national and user-inputted local values), and calculates costs based on the units per ingredient used [59, 84]. We will use CostOut to generate descriptive statistics describing typical costs (i.e., means, standard deviations) for HELM and PBIS. We will calculate total costs for each condition, and incremental costs of HELM over PBIS training and technical assistance only. We also will provide cost breakdowns to help administrators understand the budget implications of HELM, including personnel versus other direct expenses and start-up versus maintenance costs. Finally, we will conduct sensitivity analyses to examine the robustness of our cost estimates by identifying areas of uncertainty in measuring the units and prices for our ingredients, and then calculating costs across a range of plausible values [85, 86].

We also will use CostOut to calculate the cost-effectiveness of HELM versus PBIS [87]. This will involve calculating a series of incremental cost-effectiveness ratios for each student outcome (social, emotional, behavioral, academics) and PBIS implementation outcome (fidelity). Finally, we will again use sensitivity analyses to examine the robustness of our cost-effectiveness results, both across the ranges of costs examined and across plausible effectiveness estimates (i.e., 95% CIs for student and implementation outcomes).

